### Treatment Group

Patients randomized to the treatment (PRISM+usual care) group will complete the first PRISM session within ~45 days of enrollment. Patients will complete the PRISM sessions remotely using a HIPAA (Health Insurance Portability and Accountability Act)-complaint videoconferencing platform. Each session will be scheduled approximately 1-2 weeks apart but must be completed within 45 days of the previous session. We will invite each patient-parent dyad to participate in an optional 30-minute semistructured interview (see Multimedia Appendix 2 for the interview guide) that will ask about their thoughts regarding PRISM, including background, timing, duration, attendance, content, sessions, and overall satisfaction. Participants will be purposively selected to enrich the cohort for those with early dropout and ensure representation of a variety of ages, races, and ethnicities. These interviews will be conducted by a study staff member other than the PRISM coach, and they will be audio-recorded and transcribed verbatim for qualitative assessment. Participants will be paid US $25 each for their time and completion of semistructured interviews.

### Control Group

This is the usual care group. This group will be assigned online questionnaires, as described earlier. Control group participants will not receive the PRISM intervention but will receive usual care. Although adolescent participants cannot be actively engaged in CBT at the time of enrollment, they will be allowed to start any type of mental health treatment recommended as part of their treatment plan for their CMP at any point during the study. Additionally recommended as part of usual care will be cardiovascular exercise and desensitization, which may include formal physical and occupational therapy. See Figure 3 for a comprehensive description of study visit activities and the timeline for both study arms.

**Figure 3 figure3:**
[figure not shown]
Schedule of study enrollment, interventions, and assessments. EMR: electronic medical record; FDI: Functional Disability Inventory; K6: Kessler-6 Psychological Distress Scale; PRISM: Promoting Resilience in Stress Management; PROMIS: Patient-Reported Outcomes Measurement Information System.

### Statistical Analysis

The primary objective of this study is to determine whether PRISM, along with usual care, reduces functional disability more than usual care alone. The primary outcome or measure of efficacy is the FDI score at 3 months postrandomization (control group) or postintervention. The secondary efficacy outcomes are patient psychological distress (as measured with the K6), as well as the patient-reported pain intensity (as measured with the PROMIS Pediatric Numeric Rating Scale v1.0 – Pain Intensity). The secondary objectives are to determine a reduction in pain intensity and psychological distress with PRISM at intervention completion; determine reductions in functional disability, pain intensity, and psychological distress with PRISM at 6 months postintervention; evaluate potential patient- and caregiver-level moderators of PRISM; examine implementation outcomes (feasibility, acceptability, appropriateness); and identify facilitators of and barriers to engagement in PRISM.

The study team plans to publish the study findings in a peer-reviewed pediatrics, psychology, or rheumatology journal to disseminate the findings. No individually identifiable protected health information will be published. Summary results will be available on ClinicalTrials.gov.

#### Quantitative Data

Quantitative measures will be used to assess the primary and secondary efficacy outcomes, moderators of PRISM, and implementation outcomes. Demographics and baseline clinical characteristics will be summarized by standard descriptive summaries (eg, means and SDs for continuous variables, such as age, and percentages for categorical variables, such as gender). The primary analysis will use an intention-to-treat (ITT) approach to mitigate confounding from nonrandom participant attrition. We anticipate a total of 100 evaluable subjects. To ensure valid randomization, we will assess demographic and clinical features, along with baseline measures of outcomes, such as physical function, pain intensity, and psychological distress, and compare the intervention to the control arm. The primary outcome will be functional disability (FDI score) assessed at the end of the intervention (month 3). The key predictor is PRISM. Secondary outcomes will include the FDI score at the conclusion of the observation period (month 9, 6 months postintervention) and psychological distress (K6 total) and pain intensity (PROMIS Pediatric Numeric Rating Scale v1.0 – Pain Intensity) at both 3 and 9 months.

Assuming balanced arms postrandomization, we will evaluate the differences in clinical outcomes between the 2 arms at months 3 and 9 using 2-sample Student *t* tests. Longitudinal changes from month 3 to month 9 will be assessed using MANOVA (multivariate analysis of variance) and linear mixed effects models to account for within-subject correlation due to repeated measures. The linear mixed effects model can additionally adjust for a few known prognostic covariates, such as fulfillment of criteria for juvenile FM. Similar analyses will examine outcomes of psychological distress and pain intensity separately.

Linear regression will be conducted to assess the association between the change in FDI scores and changes in the intervention targets, adjusted for baseline covariates of interest. These analyses will be repeated to examine correlations between changes in secondary outcomes (pain intensity and psychological distress) and hypothesized intervention targets at month 3, and we will conduct multivariable linear regression models, adjusting for covariates of interest.

Furthermore, we will explore adolescent- and caregiver-level moderators of intervention effects, guided by an intersectionality framework [59]. For instance, we will investigate whether age moderates the intervention’s impact on functional disability by including the age × intervention interaction in the linear mixed effects regression model. If the interaction is significant, we will interpret it by plotting simple regression lines for younger (12-14 years) and older (15-16 years) adolescents. If PRISM proves more beneficial for younger participants, future studies may focus on this age group to maximize intervention effects. Additionally, we will evaluate whether biological sex moderates the intervention’s impact, ensuring adequate inclusion of male participants, given the predominance of females in the population with CMP [60].

Analyses will include calculation of eligibility, recruitment and attrition rates, and power considerations for the future full-scale RCT and evaluation of treatment fidelity. We will report the number of eligible subjects approached, the proportion of those subjects enrolled in the study, and the mean percentage of required sessions (PRISM 1-4 sessions + “coming together” session) attended among enrolled subjects. The study will be defined as feasible (binary) if the recruitment rate is ≥60%, the completion rate of all sessions among enrolled subjects is ≥70%, and the mean FIM score is ≥4. The intervention will be acceptable and appropriate if the mean AIM and IAM scores are ≥4 each. Intervention satisfaction (including session-specific and overall intervention satisfaction) will be reported as mean scores from the 5-point Likert scale (1=very dissatisfied to 5=very satisfied).

With a sample of 130 patient participants and an assumed ~20% attrition rate, we have more than 80% statistical power to detect a difference down to 5 points in the FDI between the intervention and control arms, given a prespecified mean FDI score of 26.9 (SD 11.8) and a significance level of .05 for the Student *t*-test. Table 1 lists the detectable differences (DDs) for the outcomes of interest, as well as the minimal clinically important difference (MCID) for each measure. The effect sizes of CBT on the FDI in similar patient populations have been strong to moderate (0.8-0.9), with between-group differences in the FDI score of 5.39 (95% CI 1.57-9.22). Therefore, we will be adequately powered for the primary outcome [61,62].

**Table 1 table1:** DDs^a^ in mean instrument scores between groups, given 80% power and a 5% type I error rate (N=100^b^).

Outcome (instrument)	Sample mean (SD)^c^	MCID^d^	DD
Physical function (FDI^e^)	26.9 (11.8)	8.0	5.0
Pain (PROMIS^f^ Pediatric Numeric Rating Scale v1.0 – Pain Intensity)	6.2 (2.3)	2.0	0.9
Psychological distress (K6^g^)	9.1 (6.0)	3.0^h^	2.4

^a^DD: detectable difference.

^b^Anticipated dropout rate of ~20% (total=130), resulting in 100 evaluable subjects.

^c^Sample means from preliminary data.

^d^MCID: minimal clinically important difference.

^e^FDI: Functional Disability Inventory.

^f^PROMIS: Patient-Reported Outcomes Measurement Information System.

^g^K6: Kessler-6 Psychological Distress Scale.

^h^Half the SD of mean baseline scores.

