**Methods:**

The Resilience Coaching for Adolescents with Chronic Musculoskeletal Pain pilot study is an investigator initiated, 2-arm, randomized controlled trial (RCT) of PRISM in the interdisciplinary management of CMP among adolescents. The study will compare usual care versus PRISM+usual care among adolescents newly diagnosed with CMP in the outpatient setting. One caregiver per patient will also be enrolled. The control group will receive usual care with no specific intervention. The treatment arm will receive PRISM, which is a remotely delivered, 1-on-1resilience coaching program, consisting of 4 required skill-based sessions and an optional final session. Sessions will be delivered every 1-2 weeks, lasting about 3 months in total. The primary outcome is the Functional Disability Inventory (FDI) score at 3 months postrandomization. The secondary objectives are to evaluate potential patient- and caregiver-level moderators of PRISM and identify facilitators of and barriers to engagement in PRISM. The estimated sample size is 65 patient-caregiver dyads per group, for a total of 130 dyads.

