### Medical Record Review and Questionnaires

Each enrolled participant’s medical chart will be reviewed by a study team member for information relevant to the study, including demographics, previous diagnoses, family medical history, previous surgeries, pain-related symptoms, and past treatment. Both members of each dyad will complete questionnaires at 0 months/time of enrollment; 3 months postenrollment or, if in the treatment group, immediately after intervention completion; and 9 months postenrollment. Questionnaires will be completed using an online REDCap survey. Participants will get 45 days to complete each set of questionnaires. Reminder emails or text messages (depending on participant preference) will be sent once a week to ensure completion, and reminder calls will be made a maximum of 3 times. Participants will be compensated for their time and completion of surveys. Caregivers will be paid US $20 for completion of survey 1, US $40 for completion of survey 2, and US $20 for completion of survey 3. Patient participants will be paid US $25 for completion of survey 1, US $50 for completion of survey 2, and US $25 for completion of survey 3. Should subjects request early termination, we will enumerate the next study survey as the final study survey and compensate participants with US $10 for completion of the final surveys. Next, we describe the study measures included in the questionnaires.

The patient measures are as follows:

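### ITT is credited with mitigating nonrandom attrition, but the named month-3 t test is an available-case comparison of about 100 of 130 randomised patients

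*Protocol article*

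**What the plan says.** Four statements in the protocol article bear on this point.

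- **Principle.** Quantitative Data: "The primary analysis will use an intention-to-treat (ITT) approach to mitigate confounding from nonrandom participant attrition". The next sentence reads "We anticipate a total of 100 evaluable subjects".
- **Test.** Same section, on the premise that randomisation has balanced the arms: "we will evaluate the differences in clinical outcomes between the 2 arms at months 3 and 9 using 2-sample Student" t tests. The primary outcome is FDI at month 3, so this is the test for the primary contrast.
- **Numbers.** The abstract says "The estimated sample size is 65 patient-caregiver dyads per group, for a total of 130 dyads". A footnote to Table 1 says "Anticipated dropout rate of ~20% (total=130), resulting in 100 evaluable subjects", and the power statement is for the Student t test after that loss.
- **Mixed model.** "Longitudinal changes from month 3 to month 9 will be assessed using MANOVA (multivariate analysis of variance) and linear mixed effects models". The same type of model reappears for the age-by-intervention moderator analysis. It is not named for the month-3 arm comparison.

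**The concern.** The article gives ITT a job that it cannot do. Analysing patients as randomised prevents bias from reclassifying or excluding those who did not adhere. It does not produce an FDI score for a patient who never returned the month-3 survey, and a t test on month-3 FDI has no place for that patient. The plan describes attrition as nonrandom, relies on ITT to deal with it, and names a test that leaves it untouched.

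The month-3 contrast is the headline result and is meant to inform a larger multisite trial. If loss works differently in the two arms, the reported difference describes the patients who answered rather than those who were randomised, yet it would carry the ITT label. Equal selection cannot simply be presumed. Only the PRISM arm attends sessions, and in that arm the second survey may be timed by completion of the intervention (Medical Record Review and Questionnaires).

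**Working it through.** **Inputs.** Randomised: 130, 65 per arm (abstract). Evaluable: 100 (Quantitative Data; Table 1). Loss: about 20% (Table 1 footnote). Target difference: 5 FDI points (Quantitative Data). The gap sizes and the splits of loss by arm used below are my assumptions; the documents give none.

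**Step 1: the plan's own figure.** 130 × (1 − 0.20) = 104. The stated 100 implies (130 − 100)/130 = 23.1% loss. The article rounds down from 104, and I use its 100. About 30 patients are expected to have no usable outcome, or 15 per arm if loss is even, leaving 50 against 50.

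**Step 2: what the named test uses.** A two-sample t test on month-3 FDI takes only patients with that score. A PRISM patient who stops sessions but answers the survey stays in the PRISM arm. A patient in either arm who does not answer is absent. The comparison is therefore available-case.

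**Step 3: when that biases the contrast.** For each arm, let m be the fraction missing and g the mean FDI of missing patients minus that of observed patients. The mean over everyone randomised to the arm is the observed mean + m × g. Taking PRISM minus control:

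observed difference − all-randomised difference = m(control) × g(control) − m(PRISM) × g(PRISM)

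This is zero when the two products are equal, even if missingness depends on outcome.

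**Step 4: illustration under assumed gaps.** I take higher FDI as worse, so a negative entry means that the benefit of PRISM is overstated.

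| Missing, PRISM / control | Where missing patients are worse | Gap 5 | Gap 10 |
|---|---|---|---|
| 15/65, 15/65 | both arms alike | 0 | 0 |
| 20/65, 10/65 | both arms alike | −0.77 | −1.54 |
| 15/65, 15/65 | PRISM only | −1.15 | −2.31 |
| 15/65, 15/65 | control only | +1.15 | +2.31 |

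For example, row three is −(15/65) × 5 = −1.15, and row two is (10/65 − 20/65) × 5 = −0.77. At the stated 20% loss (13/65), row three becomes −1.0 and −2.0.

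**Step 5: does the mixed model already cover this?** As described it addresses change from month 3 to month 9, and moderators. Baseline surveys are completed before randomisation (Recruitment and Randomization), so every randomised patient should have a baseline FDI that could inform the month-3 contrast. The t test does not use it.

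**The case against.** The strongest reply is that this is a condensed article. Imputation and sensitivity analyses normally sit in the full protocol or analysis plan, which are not shown. A t test can be run on imputed data, and 100 evaluable is a planning number rather than a definition of the analysis set. This stands as far as any complaint of omission goes, and none is made here. What remains is a positive statement: the article credits ITT with mitigating attrition, names an unadjusted t test, and sizes it on patients left after dropout. That credit is misplaced whatever another document adds.

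A reader might infer more than the documents support:

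- **That this is a completers' analysis, or that ITT protects against nothing.** No passage ends surveys for a patient who only stops sessions, so ITT does protect against non-adherence where the survey is answered.
- **That the t test is valid only if data are missing completely at random.** Step 3 shows otherwise for an arm contrast: selection that is alike in both arms cancels.
- **That the early-termination rule drives loss from the PRISM arm.** The rule, "Should subjects request early termination, we will enumerate the next study survey as the final study survey", applies to both arms. For someone leaving before month 3, the next survey is the one that holds the primary outcome, so the rule can help to retain it. The lower payment for that survey does not establish loss that differs by arm. Weekly reminders and up to three calls also work against loss.
- **That the effect of PRISM will be overstated by a known amount.** The gaps are assumed, and the sign reverses if the gap lies in the control arm.

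A further objection concerns the remedy. A missing-at-random model will not recover outcome-dependent loss. That is correct, and it is why the fix includes a delta-adjusted analysis.

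**Conclusion.** The point holds in a limited form. The article assigns protection against attrition to ITT, while its named month-3 comparison is an available-case t test expected to omit about 30 of 130 randomised patients (23.1%). The protection claimed is not delivered by the method stated.

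The bias, if any, has unknown size and direction. It needs a between-arm difference in the product of missing fraction and outcome gap. Under the assumed gaps of 5 to 10 points it runs from zero to about 2.3 points either way, against the 5-point target. Those figures show exposure and are not a forecast.

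The conclusion assumes that the t test is run on observed scores, as the article's sizing implies. If an analysis plan specifies imputation for the primary contrast, the remaining fault is the sentence about ITT and its mismatch with the published method.

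**What to change.** 1. Define the primary analysis set as all randomised patients, each in the assigned arm.
2. Estimate the month-3 contrast from a likelihood-based mixed model with baseline, month-3 and month-9 FDI as responses, arm-by-visit terms, and the two stratification factors, sex and clinic. Multiple imputation using baseline data is an acceptable alternative.
3. State that this model assumes missingness at random given the data in the model.
4. Add one sensitivity analysis that shifts the unobserved month-3 scores by an arm-specific delta, because the model in item 2 does not cover loss that depends on the unseen outcome. The formula in step 3 shows how far a given pair of shifts moves the contrast.
5. Delete the claim that ITT mitigates attrition, or reword it: ITT handles non-adherence, and the model with its sensitivity analysis handles missing outcomes. If the t test is kept, call it an available-case analysis.

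The cost is a few lines of text, modest extra programming, and a modelling assumption that must be stated. No new data are needed, since FDI is already collected at all three surveys.

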**Figure 2 figure2:**
[figure not shown]
PRISM RCT recruitment, screening, and consent process. CHOP: Children’s Hospital of Philadelphia; CMP: chronic musculoskeletal pain; e-consent: electronic consent; EMR: electronic medical record; PRISM: Promoting Resilience in Stress Management; PROMIS: Patient-Reported Outcomes Measurement Information System; RCT: randomized controlled trial.

Those who are not approached at their clinic visit can be contacted retroactively via telephone and, if interested and eligible, can be e-consented via REDCap (Research Electronic Data Capture), a secure, web-based software platform designed to support data capture for research studies [24,25]. For anyone who declines participation, their reasoning is recorded in the study’s master log. Study personnel attempt to contact patient-caregiver dyads a maximum of 3 times before discontinuing recruitment efforts. Once baseline surveys are complete, the dyads will be randomly assigned to a study arm using a 1:1 allocation ratio: PRISM+usual care versus usual care.

Stratified randomization will be implemented by the study statistician in REDCap to ensure a balance in sex (male vs female) and clinic (rheumatology clinic vs interdisciplinary pain [amplified musculoskeletal pain] clinic) between the 2 study arms. The final randomization scheme will be prepared by a statistician independent of the study team to prevent bias. Study staff will not get access to randomization algorithms. Tracking of dyads and randomization will be recorded in the study’s master log.

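### The between-arm analysis is an unadjusted t test premised on balanced arms; it leaves unused the baseline scores and stratification factors that would sharpen it

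*Protocol article*

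**What the plan says.** All references are to the protocol article.

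- **Primary outcome** (Quantitative Data): "The primary outcome will be functional disability (FDI score) assessed at the end of the intervention (month 3"). This is a follow-up value, not a change from baseline.
- **Between-arm method** (Quantitative Data): "Assuming balanced arms postrandomization, we will evaluate the differences in clinical outcomes between the 2 arms at months 3 and 9 using 2-sample Student" (that is, by t test). No alternative is given for arms that are not balanced. The sample-size paragraph bases power on the same t test.
- **Baseline data** (Recruitment and Randomization): "Once baseline surveys are complete, the dyads will be randomly assigned to a study arm using a 1:1 allocation ratio". FDI, K6 and pain intensity are therefore in hand before allocation.
- **Stated use of baseline outcomes** (Quantitative Data): "To ensure valid randomization, we will assess demographic and clinical features, along with baseline measures of outcomes", in order to compare the two arms.
- **Stratification** (Recruitment and Randomization): allocation is stratified "to ensure a balance in sex (male vs female) and clinic (rheumatology clinic vs interdisciplinary pain [amplified musculoskeletal pain] clinic").
- **Other models** (Quantitative Data): "Longitudinal changes from month 3 to month 9 will be assessed using MANOVA" and linear mixed models. Covariate adjustment is optional in the mixed model, and the one example is meeting juvenile fibromyalgia criteria. Covariate-adjusted linear regressions are also planned, but they relate change in outcomes to change in the intervention targets. Age and sex are examined as moderators.

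**The concern.** A baseline measurement of the outcome usually predicts its follow-up value. A model that includes it has a smaller residual variance, so the treatment effect is estimated with a smaller standard error from the same participants. Factors used to stratify the randomization are normally carried into the analysis for the same reason. Here the month-3 and month-9 comparisons use neither.

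Two things are at stake. The first is precision, in a trial of about 100 evaluable adolescents. The second is clarity. The t test is introduced on the assumption that the arms are balanced, and the same section describes a between-arm look at baseline features. The text does not say what is done if that look is unfavourable. After proper randomization baseline differences arise by chance, so the look cannot show whether the randomization was valid. Fixing the covariates beforehand makes the question irrelevant.

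**Working it through.** **Inputs from the article.** FDI SD 11.8, significance level .05, Student t test, 130 enrolled, about 20% attrition, 100 evaluable (50 per arm), 5-point target, MCID 8.0 points (sample-size paragraph and Table 1).

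**Assumptions.** Two-sided test, because sidedness is not stated. SD 11.8 at both baseline and month 3. A baseline-to-month-3 correlation r between 0.3 and 0.7, because the article gives none.

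**Step 1: the plan's own figure.** SE = SD × √(2/n) = 11.8 × √(2/50) = 2.36. The noncentrality is 5/2.36 = 2.12 on 98 degrees of freedom. Power by the noncentral t is 55%, against the stated figure of more than 80%. It is 57% at 52 per arm (130 × 0.8 = 104) and 67% at 65 per arm with no attrition. The difference detectable with 80% power at 50 per arm is 6.7 points, not 5.0. The stated power does not reproduce. That is a separate correction, but 55% is the right starting point here.

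**Step 2: adjust for baseline FDI.** Residual SD = 11.8 × √(1 − r²), with 50 per arm. The last column is 1/(1 − r²), the factor by which the sample would have to grow for the unadjusted test to match.

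| r (assumed) | Residual SD | Power for 5 points | 80%-power difference | Equivalent sample factor |
|---|---|---|---|---|
| unadjusted | 11.80 | 55% | 6.7 | 1.00 |
| 0.3 | 11.26 | 59% | 6.4 | 1.10 |
| 0.4 | 10.81 | 63% | 6.1 | 1.19 |
| 0.5 | 10.22 | 68% | 5.8 | 1.33 |
| 0.6 | 9.44 | 75% | 5.3 | 1.56 |
| 0.7 | 8.43 | 84% | 4.8 | 1.96 |

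The degrees of freedom spent on three covariates (95 instead of 98) do not alter these rounded figures. Reaching 80% power for 5 points by baseline adjustment alone needs r of about 0.66.

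**Step 3: chance imbalance.** If SD 11.8 applies at baseline, the standard error of the baseline FDI difference between arms is also 2.36. Given an imbalance of one standard error, the unadjusted month-3 difference is expected to move by r × 2.36, which is 1.2 points at r = 0.5. The t test's standard error already allows for such imbalances on average. Adjustment removes the part that baseline predicts.

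**Step 4: the MCID.** For 8 points, power at 50 per arm is 92% unadjusted and 97% at r = 0.5.

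**Step 5: do the other models fill the gap?** No. The mixed model is described for change from month 3 to month 9, the regressions concern intervention targets, and the moderator analyses concern interactions. None is presented as the month-3 arm comparison adjusted for baseline FDI, sex and clinic.

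**What cannot be computed.** The article gives no association of sex or clinic with FDI, so no gain from the strata can be quantified.

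**The case against.** The strongest defence is that nothing here is invalid. After randomization the unadjusted t test is unbiased, its standard error covers chance imbalance, and ignoring stratification factors tends to make it conservative. This stands, and it limits the point to efficiency.

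A reader might infer that the plan lets a balance check choose the analysis. The article does not support that. It gives no threshold, no decision rule and no alternative method, and the baseline comparison is not said to select anything. The proviso can be read simply as a stated assumption. What remains is loose wording that leaves a question open.

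A reader might also infer that adjustment appears nowhere except as an option in the mixed model. That is too strong, because the regressions on intervention targets adjust for covariates too. They do not estimate the treatment contrast.

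The gain depends on an assumed correlation and is small at r = 0.3 (59% against 55%). Against the 8-point MCID the t test already has 92% power. Both are true and belong beside the 5-point figures.

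Finally, an article may leave covariate lists to an analysis plan that is not shown. That would answer mere silence. Here the article names the unadjusted test and powers the trial on it, so an adjusted primary analysis elsewhere would have to be reconciled with this text.

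**Conclusion.** The point holds as one of precision and wording and should be corrected. The planned comparison leaves out baseline outcome scores and the stratification factors, all of which are available at no cost. For 5 FDI points at 50 per arm, baseline adjustment would raise power from about 55% to between 59% and 84% for r from 0.3 to 0.7. The 80%-power difference would fall from 6.7 to between 6.4 and 4.8. These figures rest on SD 11.8, a two-sided test and an assumed r; no gain is claimed for sex or clinic.

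It would be wrong to conclude that the primary estimate is systematically biased. Nor should adjustment be taken to rescue the stated power: it does so only if r is about 0.66 or more, and the power statement and Table 1 need their own correction.

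**What to change.** 1. Make the primary analysis a linear model of month-3 FDI on arm, baseline FDI, sex and clinic, or the equivalent month-3 contrast from a mixed model. Prespecify it to apply whatever balance is observed.
2. Use the same form for month-9 FDI, and for K6 and pain at months 3 and 9, each with its own baseline score.
3. Delete the proviso about balanced arms. Report baseline characteristics by arm descriptively, and drop the claim that comparing them checks whether the randomization is valid.
4. Keep the unadjusted t test as a supportive analysis.
5. When power is restated, give the assumed baseline-to-month-3 correlation and its source.

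The cost is a wording change in the protocol and analysis plan, made before any comparison by arm is seen. It needs no new data, participants or visits.

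### The month 3-to-9 model cannot by itself show benefit at 9 months, and the t tests that can do so leave out the baseline score and the randomisation strata

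*Protocol article*

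**What the plan says.** All references are to the protocol article.

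- **Objective** (Statistical Analysis): one secondary objective is to "determine reductions in functional disability, pain intensity, and psychological distress with PRISM at 6 months postintervention".
- **Endpoints** (Quantitative Data): the primary outcome is "functional disability (FDI score) assessed at the end of the intervention (month 3"). At month 9 the FDI endpoint is the score itself, not a change score. Distress (K6) and pain intensity are assessed at both visits.
- **Arm comparison** (Quantitative Data): the plan reads "we will evaluate the differences in clinical outcomes between the 2 arms at months 3 and 9 using 2-sample Student", meaning the *t* test of that name. The condition attached to it is "Assuming balanced arms postrandomization". No covariate is named for these tests.
- **Longitudinal analysis** (Quantitative Data): "Longitudinal changes from month 3 to month 9 will be assessed using MANOVA (multivariate analysis of variance) and linear mixed effects models". The mixed model may also adjust for a few prognostic covariates. Juvenile fibromyalgia status is the example given; the baseline score is not named.
- **Baseline data** (Medical Record Review and Questionnaires): "Both members of each dyad will complete questionnaires at 0 months/time of enrollment; 3 months postenrollment", and again at 9 months. For the arm comparison, the only stated use of the baseline outcome scores is to check that randomisation worked.
- **Strata** (Recruitment and Randomization): allocation is 1:1, stratified by sex and clinic. Neither factor appears in a stated arm comparison.

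**The concern.** The longitudinal analysis is the only arm analysis described that handles repeated measures and covariates, and its window opens after the treatment has been delivered. A contrast in change from month 3 to month 9 asks whether the gap between arms widened or narrowed after the intervention ended. The objective asks whether PRISM patients are better off 6 months after it. If the contrast were read as the 9-month efficacy result, a lasting benefit would look like nothing.

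Efficacy at both visits, including the primary outcome at month 3, therefore rests on t tests that set aside the baseline score of the same instrument and both stratification factors. In a trial of this size that affects the width of the confidence interval and how far a chance baseline difference carries into the estimate.

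**Working it through.** **Inputs from the article.** 130 dyads randomised 1:1, about 100 evaluable, hence 50 per arm; FDI SD 11.8; difference 5 points; significance level .05 (Quantitative Data and Table 1).

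**Assumed.** Two-sided testing; 50 per arm at each visit; the same SD at every visit; within-person correlation ρ between visits of 0.3, 0.5 or 0.7. The article gives no correlation.

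**1. The plan's own power figure.** The standard error of the arm difference is 11.8 × √(2/50) = 2.36. Power = Φ(5/2.36 − 1.96) = Φ(0.159) = 56% (exact noncentral t: 55%). One-sided it is 68%; with all 65 per arm, two-sided, it is also 68%. The stated figure of more than 80% is not reproduced. With 100 per arm, power is 85% and the detectable differences are 4.7, 0.91 and 2.38, close to the 5.0, 0.9 and 2.4 in Table 1. That looks as if the total was entered per arm. It is a separate matter; here 56% is the starting point.

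**2. What the month 3-to-9 contrast measures.** Write δ3 and δ9 for the arm differences (PRISM minus usual care; negative is benefit). The arm-by-time contrast is δ9 − δ3.

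- Benefit of 5 points at both visits: (−5) − (−5) = 0.
- Benefit of 5, then 3: (−3) − (−5) = +2. This points towards usual care although PRISM is still 3 points better.

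These patterns are illustrations, not figures from the article. At ρ = 0.5 the contrast has SD 11.8 × √(2 × 0.5) = 11.8 and standard error 2.36. A 2-point contrast would then be significant in about Φ(2/2.36 − 1.96) = Φ(−1.11) = 13% of trials.

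In 10,000 simulated trials per correlation, with a 5-point benefit at both visits, the tests rejected as follows:

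| Test | ρ = 0.3 | ρ = 0.5 | ρ = 0.7 |
|---|---|---|---|
| Arm-by-time contrast, month 3 to 9 | 5.2% | 5.0% | 4.9% |
| Planned t test at month 9 | 55% | 57% | 55% |
| Arm effect averaged over months 3 and 9 | 74% | 68% | 62% |
| MANOVA arm test on both visits | 63% | 58% | 51% |
| t test on change, baseline to month 9 | 42% | 56% | 78% |

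The contrast rejects at the significance level, as it must when its true value is zero. The month-9 t test still targets the full 5 points.

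**3. What the baseline score adds.** With baseline as a covariate (ANCOVA), the residual SD is 11.8 × √(1 − ρ²), and power = Φ(5/SE − 1.96).

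| ρ | Residual SD | SE | Power |
|---|---|---|---|
| not used | 11.80 | 2.36 | 56% |
| 0.3 | 11.26 | 2.25 | 60% |
| 0.5 | 10.22 | 2.04 | 69% |
| 0.7 | 8.43 | 1.69 | 84% |

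The same formula applies at month 3 and month 9, with ρ the correlation of that visit with baseline.

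**4. Chance imbalance.** Under correct randomisation the baseline arm difference also has standard error 2.36. Given a baseline difference b, the unadjusted estimate shifts on average by ρ × b. For b = 2.36 that is 0.7, 1.2 or 1.7 FDI points at ρ = 0.3, 0.5 or 0.7. A linear baseline term removes this shift. The article does not show how strongly sex and clinic predict the FDI, so no size is given for the strata.

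**The case against.** The strongest reply is that the 9-month objective is tested directly. The sentence before the longitudinal one plans a between-arm t test at month 9, on an endpoint defined as a level. Under 1:1 randomisation that test is unbiased without a baseline term. This stands. A reader might infer that a durable effect would appear as no effect in the plan as a whole; the documents do not support that. Nor does the article say which term of the mixed model or MANOVA is tested. An arm main effect, or a MANOVA arm test on both visits, would also detect a durable effect, as the simulation shows.

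A reader might also infer that the moderator analysis targets the wrong contrast, because it sits in the mixed model. The text describes "including the age × intervention interaction in the linear mixed effects regression model", a two-way term without time. It is not shown to be moderation of waning.

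Change from month 3 to month 9 is a legitimate durability question, and the Introduction gives durability as the reason for the 9-month survey. The mixed-model covariate list is given by example, so the baseline score is not excluded. The article does not say that the t tests are complete-case, and nothing in it shows that MANOVA has to be removed.

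Finally, using baseline does not always help. A simple change score is weaker than the plain t test at ρ = 0.3 (42% against 55%) and about equal at 0.5. Covariate adjustment gains at all three correlations, though by only about 4 percentage points at 0.3.

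What the reply leaves untouched is that the longitudinal window omits month 0, and that no stated arm comparison uses the baseline score or the strata.

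**Conclusion.** The point holds as one of precision and interpretation, not of validity. The arm-by-time contrast from month 3 to month 9 describes waning or late gain and should not be read as evidence for or against benefit at 9 months. The t tests at months 3 and 9 address the right differences and are valid under randomisation, but they discard baseline information already collected and ignore sex and clinic.

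For a 5-point FDI effect, power is about 56% unadjusted, against 60%, 69% or 84% with baseline ANCOVA. This rests on 50 evaluable per arm, SD 11.8 at each visit, two-sided testing at .05, and assumed correlations of 0.3, 0.5 and 0.7. The gain depends mainly on the correlation, which the article does not give. The t tests need no assumption of balanced arms to be valid; adjustment limits the effect of any chance imbalance in baseline score, sex or clinic.

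**What to change.** For each outcome (FDI, K6, pain intensity), fit one linear mixed model to the follow-up visits with the baseline score as a covariate, or include month 0 as a visit with arm means constrained equal. Add sex, clinic and arm-by-visit terms. Name the arm differences at month 3 and month 9, with confidence intervals, as the efficacy estimates; the month-3 FDI difference remains primary. Report month 9 minus month 3 only as a description of durability. The t tests can stay as an unadjusted supplement, and MANOVA need not be dropped if its role is stated.

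The cost is a wording change in the protocol or analysis plan, made before the arms are compared. Baseline scores, sex and clinic are already recorded, so no visit, questionnaire or participant is added.
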